### Data collection

Demographic and study endpoint data will be collected using anonymous surveys distributed to participating residents, relatives and staff members at the intervention and control nursing homes at baseline, post-intervention, and at six-month follow-up. Demographic data include participants’ age, gender and first language. For residents, demographic data will also include assessments of their ability to perform personal activities of daily living, measured by The Katz ADL-index [47], cognitive impairment measured by the Gottfries cognitive scale [48], and neuropsychiatric symptoms as measured by the Neuropsychiatric Inventory - Nursing Home version [49]. For staff, demographic data will also include education and employment. For relatives, demographic data will also include their relation to the resident and how often they visit the nursing home.

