### Inclusion criteria, recruitment, and study sample

To be included in the study, nursing homes must meet the following inclusion criteria: a) managers expressing a need and willingness to participate and support the intervention, b) having about 50 resident beds, and c) employing at least 50 staff members. The recruitment of eligible nursing homes will be purposively conducted at each international site using the researchers’ clinical networks. Nursing home managers will be given/provided verbal and written information on the eligibility criteria, the purpose of the study, the intervention and its implementation process. Before commencing the study, written information and a formal invitation to participate in the data collection will be given to all staff members at the nursing homes where managers have consented to participate.

Participants will be included continuously during the intervention, with the following inclusion criteria: residents need to have lived in the nursing home for >1 month by the time of data collection; relatives need to visit the nursing home on a regular basis (>1/month); staff need to work in the nursing home on a temporary and or permanent basis (>1 month contract), and have been working >1 month in the nursing home by the time of data collection. The goal will be to include at least 900 participants in the study; 300 residents, 300 relatives, and 300 staff members. All eligible persons will be given written information on the purpose and outline of the study, and will be given the opportunity to ask the researchers questions regarding the study throughout the study period.

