### Power calculation

Sample size calculations have been made based on a medium effect size of 0.30, a two-sided significance level of 0.05 and a power of 0.85. Calculations for the primary *resident* endpoint was based on unpublished results of TOPAS mean values of 154 and SD 22, indicating that a sample of 150 residents from each group would be sufficient to detect pre-post intervention differences of 6.2. Calculations of the primary *relative* endpoint was based on a previously reported Pyramid questionnaire mean of 76 and SD 21 for overall satisfaction in similar context [57], which indicates that a sample of 150 relatives from each group would be sufficient to detect significant pre-post intervention mean differences of at least 8.7. Calculations of the primary *staff* endpoint was based on a previously reported MJS mean of 81 and SD of 14 for job satisfaction in similar context [34], which indicates that a sample of 150 staff from each group would be sufficient to detect significant pre-post intervention mean differences of at least 3.4. Therefore, a total of at least 900 participants will be recruited.

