### Statistical analyses

Sample characteristics will be explored using descriptive statistics, and standard analyses adjustments will be made to adjust for baseline differences between groups should such exist. In cases of missing data, sensitivity analyses will be performed to compare results with complete case analyses [58], and different options for imputation will be considered and discussed with statisticians before making a final decision. Differences between intervention and controls will be tested with *χ*2 tests for categorical variables, and independent sample *t*-test for continuous variables. General linear mixed models will be used to test effects of the interventions on primary and secondary endpoints. Potential confounders will be included as covariates. *P*-values of *<*0.05 will be regarded as statistically significant and effect sizes of *>*0.3 will be regarded as clinically significant. IBM SPSS Statistics for Windows, version 22.0 (Armonk, NY, USA: IBM Corp. Released 2013) will be used to analyse data.

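### Surveys are described as anonymous at all three waves with no linkage code, while the sample size rests on pre-post differences that unlinked waves of 150 per arm would not detect at the planned power

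*Protocol article*

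**What the plan says.** Under Data collection: "Demographic and study endpoint data will be collected using anonymous surveys distributed to participating residents, relatives and staff members" in both arms "at baseline, post-intervention, and at six-month follow-up". Neither this section nor any other part of the article mentions a participant code, a key or another way to match forms between waves. None rules one out either.

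Under Inclusion criteria, recruitment, and study sample, the cohort is open: "Participants will be included continuously during the intervention". The Discussion counts high turnover of staff and of residents among the difficulties of trials in this setting.

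Under Power calculation, the sample size is "based on a medium effect size of 0.30, a two-sided significance level of 0.05 and a power of 0.85". For residents it uses "unpublished results of TOPAS mean values of 154 and SD 22" and concludes that "a sample of 150 residents from each group would be sufficient to detect pre-post intervention differences of 6.2". The relatives' and staff calculations are worded in the same way, for example "150 relatives from each group would be sufficient to detect significant pre-post intervention mean differences" of at least 8.7. The staff difference is 3.4.

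Under Statistical analyses: "General linear mixed models will be used to test effects of the interventions on primary and secondary endpoints". Potential confounders enter as covariates, and baseline differences between the groups are to be adjusted for if they exist.

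**The concern.** In its ordinary sense, an anonymous form cannot be matched to another form from the same person. If the surveys run that way, the three waves are partly overlapping cross-sections with the overlap hidden.

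Two things are lost:

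- **Precision.** A person's own baseline score cannot be used, either through a change score or as a covariate.
- **Control of turnover.** With six purposively recruited homes, no randomisation described and people entering and leaving, a shift in the mean may reflect a change in who answered. Unlinked data cannot tell this apart from change in the people who stayed.

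All three primary endpoints are affected. The loss cannot be reliably repaired later, because baseline forms collected without a code cannot be matched afterwards.

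**Working it through.** **Inputs from Power calculation.** Two-sided 0.05, power 0.85, 150 per group, SDs 22 (TOPAS), 21 (Pyramid) and 14 (MJS), stated differences 6.2, 8.7 and 3.4. The multiplier is 1.960 + 1.036 = 2.996.

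**Assumptions.** The 150 are respondents per arm at each wave. Clustering by home is ignored. The pre-post correlation r is not in the document; 0.5 and 0.7 are used.

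**Step 1: the plan's own figures.** A paired pre-post formula within one arm, with the listed SD taken as the SD of change, is 2.996 × SD / √150:

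- TOPAS: 2.996 × 22 / 12.25 = 5.4 (stated 6.2)
- Pyramid: 2.996 × 21 / 12.25 = 5.1 (stated 8.7)
- MJS: 2.996 × 14 / 12.25 = 3.43 (stated 3.4)

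Only the staff figure reproduces. It does so with a formula that needs each person's two answers to be matched.

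**Step 2: unlinked waves, difference between arms in change.** Four independent means of 150 give 2.996 × SD × √(4/150) = 2.996 × SD × 0.1633.

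**Step 3: linked waves, complete overlap.** Change score: 2.996 × SD × √(4(1 − r)/150). Baseline-adjusted: 2.996 × SD × √(2(1 − r²)/150).

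| Detectable difference | TOPAS | Pyramid | MJS |
|---|---|---|---|
| Stated in the protocol | 6.2 | 8.7 | 3.4 |
| Unlinked, difference in change | 10.8 | 10.3 | 6.9 |
| Linked change score, r = 0.5 | 7.6 | 7.3 | 4.8 |
| Linked, baseline-adjusted, r = 0.5 | 6.6 | 6.3 | 4.2 |
| Linked, baseline-adjusted, r = 0.7 | 5.4 | 5.2 | 3.5 |

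At the stated differences, the unlinked difference in change has power 0.41, 0.72 and 0.32. At the stated effect size of 0.30 its power is 0.45, and 400 per group per wave would be needed for 0.85.

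**Step 4: a simpler unlinked contrast.** Comparing the arms post-intervention only, or pre with post within one arm, gives 2.996 × SD × √(2/150) = 7.6, 7.3 and 4.8. The relatives' 8.7 is then within reach. The resident 6.2 and the staff 3.4 are not.

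**Step 5: partial overlap.** If a share p of respondents answers both waves and is linked, the variance factor for the simple change contrast is 4(1 − p·r)/150. With p = 0.5 and r = 0.5 (both assumed) it is 4 × 0.75/150 = 0.02, so the detectable differences are 2.996 × SD × 0.1414 = 9.3, 8.9 and 5.9. This lies between the unlinked row and the linked change-score row.

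**The case against.** The strongest reply is that a reader might infer that linkage is impossible, and the article does not say so. It does not define *anonymous*. A form without a name can carry a self-generated code, and such a detail may sit in the full protocol, which is not shown. The match of the staff figure to a paired formula suggests that linkage may have been intended and the word chosen loosely. This stands: the finding concerns the text as written and does not show that the design is broken.

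The following also stands:

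- Mixed models do not require person-level linkage. Repeated cross-sections can be fitted with group-by-wave terms, and the promised adjustment for baseline differences is worded at group level. No paired test or individual baseline covariate is named.
- With continuous inclusion, later entrants have no baseline value even when forms are coded.
- Linking people does not remove variation between homes, and there are only three homes per arm.
- A reader might infer that unmatched repeat responders produce false positives. For the change contrast, ignoring a positive correlation makes the standard error too large, so the result is lost power.
- Most demographic covariates, such as age, gender and first language, cannot plausibly be altered by the intervention. The worry about covariates measured after it reaches only items such as neuropsychiatric symptoms, daily living ability and visiting frequency.
- Matching residents to their own relatives serves no stated research question and is not asked for here.

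One objection stands only in part: that the unlinked figures suppose nobody answers twice. If everyone did, unmatched, the test would still use the larger standard error. The detectable difference would be 1.960 × SD × 0.1633 + 1.036 × SD × √(4(1 − r)/150). At r = 0.5 that is 9.7, 9.2 and 6.2, all above the stated values. At r = 0.7 it is 9.1, 8.7 and 5.8, so only the relatives' figure is then met.

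**Conclusion.** The concern holds for the protocol as written: no means of matching is described, and the pre-post sizing does not fit unlinked waves. For the between-arm difference in change, the unlinked detectable differences exceed the stated ones by a factor of about 1.7 (10.8/6.2), 1.2 (10.3/8.7) and 2.0 (6.9/3.4). The resident and staff targets are out of reach under each unlinked contrast examined; the relatives' target is out of reach mainly for the difference in change.

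Linkage helps but does not by itself rescue every figure. At r = 0.5 with complete overlap, the resident 6.2 and the staff 3.4 are still slightly missed after baseline adjustment; at r = 0.7 the staff figure is about met (3.5). The size of the gain rests on an assumed correlation, complete overlap and no clustering, so the real gain will be smaller. That 150 per group does not follow from the stated effect size of 0.30 by the plain two-sample formula (200 per group) is a separate matter.

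**What to change.** Before the baseline survey:

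1. Put a study code on each questionnaire, with the key held outside the analysis team. Where a key is not acceptable, use a self-generated code.
2. Under Data collection, replace *anonymous* with *coded (pseudonymised)*.
3. Under Statistical analyses, state that the mixed model has a participant random effect and keeps respondents seen at only one wave. Use baseline covariate values where they exist.
4. Restate the detectable differences for the linked contrast, with the assumed correlation and the expected overlap.

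If coding is not acceptable, say so, declare a repeated cross-sectional analysis with group-by-wave terms, and restate the detectable differences on that basis.

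The cost is a change to the form, the information letter and the ethics wording. Coded forms may also lower candour or response a little, mainly among staff, who report on their own job satisfaction and stress of conscience. The documents give no figure for that loss, and a self-generated code should limit it.

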### Study endpoints

The primary study endpoints are: residents’ thriving as measured by the Thriving of Older People Assessment Scale [11], relatives’ satisfaction with care as measured by the Pyramid questionnaire [50], and staff job satisfaction as measured by the Measure of Job Satisfaction scale [51].

The secondary study endpoints consist of the perceived caring environment as measured by the Person-centred Climate Questionnaire-patient, −family, and -staff versions [52–54]. Relatives’ experiences of visiting the nursing home will be measured by 12 study specific questions (e.g. *I feel welcome when I come to the nursing home; The nursing home’s physical environment is aesthetically pleasing; I have positive experiences of visiting my relative)* with answers on a scale from 0 = Totally disagree to 10 = Totally agree. Staff members’ stress of conscience will be measured by the Stress of conscience questionnaire [55] and perceived levels of person-centred care will be measured by the Person-centred Care Assessment Tool [56] . All endpoint measures have been tested for validity and reliability in relation to the study population and context. Please see Table 2 for an overview of endpoint measures.

**Table 2 Tab2:** Study endpoints and measurements

Endpoints	Measurements	Study population	Tested for reliability and validity
Primary Endpoints			
Thriving	The Thriving of Older People Assessment Scale (TOPAS)	Residents	Yes^a^
Satisfaction with care	The Pyramid Questionnaire	Relatives	Yes^a^
Job satisfaction	The Measure of Job Satisfaction (MJS)	Staff	Yes^a^
Secondary Endpoints			
Experience of the caring environment	The Person-centred Climate Questionnaire (patient/family/staff version)	Residents, relatives and staff	Yes^a^
Experience of visiting their relative and the care setting	Study specific questions	Relatives	N/A
Stress of conscience	Stress of conscience questionnaire	Staff	Yes
Person-centred care	Person-centred Care Assessment Tool (P-CAT)	Staff	Yes^a^

^a^ in relation to study population and context

### Blinding

Due to the nature of the intervention, blinding to study allocation will not be possible.

### Power calculation

Sample size calculations have been made based on a medium effect size of 0.30, a two-sided significance level of 0.05 and a power of 0.85. Calculations for the primary *resident* endpoint was based on unpublished results of TOPAS mean values of 154 and SD 22, indicating that a sample of 150 residents from each group would be sufficient to detect pre-post intervention differences of 6.2. Calculations of the primary *relative* endpoint was based on a previously reported Pyramid questionnaire mean of 76 and SD 21 for overall satisfaction in similar context [57], which indicates that a sample of 150 relatives from each group would be sufficient to detect significant pre-post intervention mean differences of at least 8.7. Calculations of the primary *staff* endpoint was based on a previously reported MJS mean of 81 and SD of 14 for job satisfaction in similar context [34], which indicates that a sample of 150 staff from each group would be sufficient to detect significant pre-post intervention mean differences of at least 3.4. Therefore, a total of at least 900 participants will be recruited.

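### The power paragraph does not follow from its own inputs: 150 per group gives about 74% power at 0.30 SD in a plain two-group comparison, not 85%, and none of the three detectable differences equals 0.30 SD

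*Protocol article*

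**What the plan says.** The Power calculation section sets one basis for all three primary endpoints. The calculations are "based on a medium effect size of 0.30, a two-sided significance level of 0.05 and a power of 0.85". It then takes the endpoints in turn, each with 150 per group:

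- Residents (TOPAS, mean 154, SD 22): "a sample of 150 residents from each group would be sufficient to detect pre-post intervention differences of 6.2".
- Relatives (Pyramid questionnaire, mean 76, SD 21): 150 per group "would be sufficient to detect significant pre-post intervention mean differences of at least 8.7".
- Staff (MJS, mean 81, SD 14): 150 per group "would be sufficient to detect significant pre-post intervention mean differences of at least 3.4".

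The recruitment target of 900 is drawn from these figures. The section gives no pre-post correlation and no SD of change. The Statistical analyses section uses the same 0.30 as a yardstick: effect sizes above "0.3 will be regarded as clinically significant". It assigns group comparisons of continuous variables to the independent-samples t-test and intervention effects to linear mixed models with covariates. The Data collection section says the surveys are anonymous.

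**The concern.** With one effect size, one alpha, one power and one group size, the difference each endpoint can detect should be the same multiple of its SD. The printed differences are not. Relatives have a slightly smaller SD than residents (21 against 22) but a larger detectable difference (8.7 against 6.2). The group size of 150 also looks too small for 85% power at 0.30 SD.

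This paragraph is the only stated basis for the 900 target. A reader of a null result for residents or staff could take it that differences of 6.2 or 3.4 points would have been found with 85% probability. On the stated inputs, a two-group comparison does not offer that.

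**Working it through.** **Inputs, all from Power calculation.** Standardised effect d = 0.30; two-sided alpha 0.05; power 0.85; n = 150 per group; SDs 22, 21 and 14; stated differences 6.2, 8.7 and 3.4. Participants are treated as independent throughout.

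**1. Trying to reproduce 150 per group at 85% power.** Two-group comparison: n per group = 2 × ((1.960 + 1.036) / d)². With d = 0.30 this is 2 × (2.996 / 0.30)² = 199.5, so 200 (noncentral t: 200.5). The stated 150 is not reproduced.

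Power at n = 150 and d = 0.30: the noncentrality is 0.30 × √(150/2) = 2.60, giving 73.8% by the normal approximation and 73.6% by the noncentral t.

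Other simple settings do not give 150 at 85% either:
- one-sided test: 160 per group, and 83% power at 150;
- 80% power, two-sided: 175 per group;
- one-group paired test with SD of change equal to the stated SD: about 100 are needed, and 150 gives 95%.

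**2. The printed differences in SD units, with two-group power at n = 150 (noncentral t).**

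| Endpoint | Stated difference / SD | 0.30 SD in points | Power at stated difference | n per group for 85% at stated difference |
|---|---|---|---|---|
| Residents | 6.2 / 22 = 0.28 | 6.6 | 68% | about 227 |
| Relatives | 8.7 / 21 = 0.41 | 6.3 | 95% | about 106 |
| Staff | 3.4 / 14 = 0.24 | 4.2 | 55% | about 305 |

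The largest ratio is 0.414 / 0.243 = 1.7 times the smallest.

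**3. What 150 per group detects at 85% power.** By the normal approximation d = 2.996 × √(2/150) = 0.346; by the noncentral t, 0.347. In points: 0.347 × 22 = 7.6, 0.347 × 21 = 7.3 and 0.347 × 14 = 4.9.

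**4. Can another formula give 6.2, 8.7 and 3.4?** Let r be the pre-post correlation.
- *One-group paired, SD of change = stated SD.* Detectable effect 0.246 SD: 5.4, 5.2 and 3.4. Only the staff figure fits.
- *Two-group change score, variance factor 2(1 − r).* Solving for r at 85% power: r = 1 − (ratio / 0.347)² / 2, which is 0.67 (residents), 0.29 (relatives) and 0.76 (staff). All three fit, but only with a different r each.
- *Baseline-adjusted comparison, variance factor (1 − r²).* Adjustment can only lower the detectable difference, and 8.7 already exceeds the 7.3 available with no covariate. The relatives figure cannot arise this way at 85% power.

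**5. Can another formula give 85% at d = 0.30 with n = 150?** Yes, with an added assumption. Baseline adjustment at r = 0.5 needs 199.5 × (1 − 0.25) = 149.6 per group, for power of about 85%. A change score needs r of about 0.63. Either reading gives detectable differences of 6.6, 6.3 and 4.2, not the printed ones.

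**The case against.** The paragraph speaks of pre-post differences, so a two-group comparison of change is a natural reading, and correlations of 0.67, 0.29 and 0.76 are all plausible values. Effects are to be tested with mixed models and covariates, not an unadjusted t-test at one time point, and baseline adjustment at r of about 0.5 does give 85% at 0.30 SD. An article may also leave a correlation or SD of change to the full protocol.

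Much of this stands, and it rules out several stronger readings:
- *That 85% power is out of reach with 150 per group.* It is not, given a suitable correlation. The 74% applies to the plain two-group comparison, which is the contrast that can be computed from the printed inputs.
- *That no formula can produce the three differences.* The change-score formula can, with a separate correlation for each endpoint. What cannot produce them is one formula with common parameters.
- *That the relatives endpoint is underpowered.* It is not: 150 per group exceeds what 8.7 points requires. The fault there is only that 8.7 is not 0.30 SD.
- *That being able to detect less than the 0.3 threshold is itself a defect.* It is not, and the article does not say which SD standardises that threshold.

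The objection does not make the paragraph consistent. The reading that yields 85% at 0.30 SD contradicts all three printed differences. The reading that yields the printed differences abandons the single effect size of 0.30. Both need within-person linkage, which anonymous surveys make doubtful unless a linking code exists that the article does not mention. Condensation is no answer either, because the point is that the printed numbers conflict with each other, not that one is absent.

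**Conclusion.** Wrong as written. For a plain two-group comparison, 150 per group falls about 50 per group short of what 85% power at 0.30 SD requires, and power is overstated by about 11 percentage points (85% against 74%). At the printed differences the shortfall is larger for residents (68%) and staff (55%); for relatives the figure is conservative (95%).

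The mismatch between one stated effect size and ratios of 0.28, 0.41 and 0.24 does not depend on the choice of test, provided that the stated SDs are the standardiser and the parameters are common to the endpoints. The power percentages do depend on that choice: they assume independent participants, 1:1 groups and no gain from baseline data. Participants are in fact grouped in six homes, so positive correlation within homes would lower power further; that is not quantified here.

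**What to change.** Keep 150 per group and rewrite the paragraph around one named contrast and one named SD for all three endpoints. Then state either:

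- power of about 74% at 0.30 SD, that is 6.6 points (TOPAS), 6.3 (Pyramid) and 4.2 (MJS); or
- detectable differences of about 7.6, 7.3 and 4.9 points at 85% power.

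If a change-score or baseline-adjusted analysis is what was meant, state the assumed pre-post correlation for each endpoint, say how anonymous surveys will be linked, and recompute the figures from those values. In either case, add that the figures treat participants as independent.

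The cost is wording only. Recruitment and analysis do not change; the figures for residents and staff become less favourable.

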## Methods

The overall aim of the U-Age nursing home study is to evaluate effects and meanings of a person-centred and thriving-promoting intervention in nursing homes. More specifically, the following research questions will be explored:Will the intervention increase resident’s thriving (primary endpoint), and positively affect their experience of the care environment (secondary endpoint)?Will the intervention increase relatives’ satisfaction with care (primary endpoint), enhance their experience of visiting their relative and the nursing home, and positively affect their experience of the care environment (secondary endpoints)?Will the intervention increase staff’s job satisfaction (primary endpoint), decrease their stress of conscience, increase the perceived level of person-centredness of care and positively affect their experience of the care environment (secondary endpoints)?What are the experiences and meanings of the intervention as described by relatives and staff?

The study is designed as a multi-centre, non-equivalent controlled group before-after study with participating sites in Victoria (Australia), Oslo (Norway) and Västerbotten (Sweden). Two nursing homes at each site have been allocated to either intervention or control, in total three intervention and three control facilities across the three international sites. Study specific surveys will be used to collect data on primary and secondary endpoints, with study endpoints being analysed post-intervention, and at six-month follow-up. Qualitative research interviews will be conducted post-intervention to illuminate experiences and meanings of the intervention as described by relatives and staff.

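### The 0.85 power claim treats 150 people per group as independent although only three whole homes per arm were allocated, and the stated figures do not deliver that power

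*Protocol article*

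**What the plan says.** The Power calculation section takes "a medium effect size of 0.30, a two-sided significance level of 0.05 and a power of 0.85" as its basis for all three primary endpoints.

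- Residents: it starts from "unpublished results of TOPAS mean values of 154 and SD 22" and concludes that "a sample of 150 residents from each group would be sufficient to detect pre-post intervention differences of 6.2".
- Relatives: it uses "a previously reported Pyramid questionnaire mean of 76 and SD 21 for overall satisfaction" and a difference of 8.7, again with 150 per group.
- Staff: it uses an MJS mean of 81 and SD of 14, and concludes that "a sample of 150 staff from each group would be sufficient to detect significant pre-post intervention mean differences of at least 3.4".

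The total of 900 is 3 populations × 2 groups × 150.

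The Methods section allocates whole homes, one pair in each country: "in total three intervention and three control facilities across the three international sites". The inclusion criteria for homes specify "having about 50 resident beds, and c) employing at least 50 staff members". So 150 per group is 3 homes × 50, with nothing added for clustering.

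In Statistical analyses, one sentence reads "Differences between intervention and controls will be tested with" and goes on to chi-square and independent-sample t-tests. The next sentence assigns the testing of intervention effects on the primary and secondary endpoints to general linear mixed models. It does not say whether home is a level in those models. Data collection states that the surveys are anonymous.

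**The concern.** Residents, relatives and staff of one home share its management, building and workforce. The primary outcomes (thriving in the place of living, satisfaction with care, job satisfaction) are closely tied to that home. The intervention also acts on the home, through staff workshops and enrichment of common areas. Responses within a home are therefore likely to be correlated, and the comparison between arms carries home-to-home variation that a formula for independent people leaves out. Six homes also leave very few degrees of freedom for estimating that variation.

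At stake is the interpretation of all three primary results. A reader who believes the 85% claim would take a null result as fair evidence that the intervention has no effect of the planned size, when the study may have had much less chance of showing one.

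**Working it through.** **Inputs.** From Power calculation: effect size d = 0.30, two-sided alpha 0.05, power 0.85, and SD/difference of 22/6.2 (residents), 21/8.7 (relatives) and 14/3.4 (staff). From Methods and the inclusion criteria: 3 homes per arm and about 50 people per home. Taking 50 for relatives as well is an assumption that matches 150 per arm. **Assumed, because the article gives no value:** ICC 0.01 to 0.10.

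**Step 1. Reproduce the stated 150 for independent people.** n per group = 2(1.96 + 1.036)²/d². At d = 0.30 this is 2 × 8.98/0.09 = 199.5, so 200 rather than 150. Power with 150 per group is Φ(d√75 − 1.96).

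| Target | d | n per group for 0.85 | Power at 150 |
|---|---|---|---|
| Stated effect size | 0.30 | 200 | 74% |
| Residents 6.2/22 | 0.28 | 227 | 68% |
| Relatives 8.7/21 | 0.41 | 105 | 95% |
| Staff 3.4/14 | 0.24 | 305 | 56% |

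The staff figure can be reproduced as a one-group before-after test with 14 taken as the SD of change: (2.996 × 14/3.4)² = 152.2, so n = 153. That is not the contrast between arms, and the same formula gives 114 for residents and 53 for relatives. No single formula tried yields 150 for all three.

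**Step 2. Add clustering, single post-intervention comparison.** Design effect = 1 + 49 × ICC; effective n per arm = 150/design effect; noncentrality = d√(effective n/2). Power comes from the normal distribution, or from the noncentral t with 6 − 2 = 4 df.

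| ICC | Design effect | Effective n | d = 0.30: normal / 4 df | Relatives: normal / 4 df | Staff: normal / 4 df |
|---|---|---|---|---|---|
| 0.01 | 1.49 | 101 | 57% / 37% | 84% / 60% | 41% / 27% |
| 0.02 | 1.98 | 76 | 46% / 30% | 72% / 49% | 32% / 21% |
| 0.05 | 3.45 | 43 | 29% / 19% | 49% / 32% | 20% / 14% |
| 0.10 | 5.90 | 25 | 19% / 13% | 31% / 21% | 14% / 10% |

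In this comparison, effective n per arm cannot exceed 3/ICC however many people each home supplies. Since 200 are needed, 85% at d = 0.30 is out of reach above ICC = 3/200 = 0.015, even by the normal approximation.

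**Step 3. Before-after contrast between arms.** The article speaks of pre-post differences. With anonymous surveys, no person-level pre-post correlation can be assumed, so the samples are treated as unlinked. Let c be the correlation of a home's effect between waves. The variance in SD units is 4[(1 − c)ICC + (1 − ICC)/50]/3. Power at d = 0.30 (normal):

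| ICC | c = 0.8 | c = 1 |
|---|---|---|
| 0.01 | 42% | 46% |
| 0.02 | 39% | 46% |
| 0.05 | 33% | 47% |

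Stable home effects cancel here, but differencing two independent samples doubles the sampling variance. A 4-df reference would lower these figures further.

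**Step 4. Type I error if home were ignored.** For the before-after contrast, error = 2[1 − Φ(1.96√((4/150)/variance))]. With c = 1 it is about 5% or slightly less at ICC 0.01 to 0.05. With c = 0.8 it is about 6%, 7%, 10% and 16% at ICC 0.01, 0.02, 0.05 and 0.10.

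**The case against.** Four points can be made for the plan.

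**Mixed models are already named for effects.** This stands, and it limits the point. A reader might infer that the t-tests and chi-square tests are the tests of effect, and that false positives are therefore inflated, to 11–42% by the single-comparison formula 2[1 − Φ(1.96/√design effect)]. The article does not support that. The paragraph opens with sample characteristics and baseline differences, so the t-test sentence can be read as a check of group comparability. A random home effect may also be set out in an analysis plan that is not shown. The 11–42% belongs to a post-only comparison, whereas the design is before-after with controls, where Step 4 applies. A random home effect would repair the type I error but not the power.

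**Not all of the shortfall is clustering.** This also stands. A reader might blame the entire gap on clustering, but Step 1 shows 74% at d = 0.30 before any ICC enters.

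**The endpoints differ.** Relatives have 95% power without clustering and 84% at ICC 0.01 by the normal approximation. That falls to 60% with 4 df, so the endpoint is the most robust but is not secure.

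**An article condenses its protocol.** This does not rescue the claim. The article prints the calculation, its inputs and its conclusion, and that printed conclusion is what fails.

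A reader might also argue from a permutation test of three against three homes, which cannot reach p < 0.05. No such test is planned and no randomisation is stated, so the argument does not apply.

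**Conclusion.** The point holds for power. The stated 0.85 is not delivered by 150 per group at an effect size of 0.30, nor for the quoted resident and staff differences as two-group comparisons, even with independent people. Allocation of three homes per arm lowers power further, to 57/46/29/19% (normal) or 37/30/19/13% (4 df) at ICC 0.01/0.02/0.05/0.10 in a post-intervention comparison, and to about 33–47% in an unlinked before-after contrast at ICC 0.01 to 0.05.

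The size of the clustering loss rests on the assumed ICC, on 50 people per home for each population and, for the before-after figures, on a home autocorrelation of 0.8 to 1. That the claim fails at d = 0.30 does not depend on the ICC.

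Inflated type I error is conditional. It would arise only if endpoints were tested with unclustered tests or with a mixed model lacking a home level. Its size would depend on how much home variation is left after before-after differencing.

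**What to change.** 1. Withdraw the 0.85 claim. Restate power for each primary endpoint as a contrast between arms, over a stated ICC range (for example 0.01 to 0.10), with degrees of freedom based on six homes. Say whether the target is the post-intervention difference or the difference in change, and whether people are linked across waves.
2. State that the mixed model for effects includes home as a level, with a home-by-time term, and country, since homes were allocated in pairs within country. State that it uses small-sample degrees of freedom, and that estimates with cluster-adjusted confidence intervals will be reported.
3. State that the t-tests and chi-square tests only describe group comparability and do not test the effect of the intervention.

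The cost is a rewritten power paragraph and a few sentences on the model. Stated power will be lower and intervals wider. No additional homes or participants are required.
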